### Sample size

2.4

For the sample size we focused on the accuracy with which the ICGA quantitative parameters will be able to predict AL. For an alpha = 0.05 and a power of 0.80, a total sample size of 54 patients is required to be able to show a statistically significant difference of the area under the curve in a receiver operating characteristic curve (ROC), provided that a leak rate of 16% is observed. Including a 10% drop out or lost to follow-up, we intent to include 70 patients.

### Study interventions

2.5

#### Surgical procedure

2.5.1

A standard MIE will be performed using the Ivor Lewis technique (intrathoracic stapled esophagogastric anastomosis). Three regions of interest (ROIs) will be marked on the stomach graft with a suture (Fig. 1):

**Figure 1 F1:**
[figure not shown]
The regions of interest during gastric tube construction.

ROI 1: well perfused control region: 2 to 3 cm proximal to the pylorus

ROI 2: clinically identified anastomotic site: study region

ROI 3: ischemic control region: in the proximal (excluded) stomach

#### ICG-based NIR perfusion imaging

2.5.2

Imaging will be performed twice: 30 minutes after the creation of the stomach graft (in the abdomen), and immediately before creation of the esophagogastric anastomosis (in the right thorax). A dose of 0.5 mg/kg of ICG (ICG-Pulsion, Pulsion Medical Systems, Munich, Germany) will be injected as an intravenous bolus. Images will be recorded starting immediately before injection until 3 minutes afterwards. Video data will be obtained with a charge-coupled device camera fitted with a light-emitting diode emitting at a wavelength of 760 nm, and the appropriate filters to detect NIR fluorescence (Visera elite II, Olympus Medical System Corp, Tokyo, Japan). The fluorescence signals are sent to a digital video processor to be displayed on a TV monitor in real time (Fig. 2).

**Figure 2 F2:**
[figure not shown]
Expected ICGA perfusion through the gastric tube. ICGA = indocyanine green angiography.

#### Hemodynamic evaluation

2.5.3

Advanced continuous hemodynamic monitoring during surgery will be performed using a PiCCO (Pulsion Medical Systems) catheter integrating a wide array of both static and dynamic data through a combination of transcardiopulmonary thermodilution and pulse contour analysis. All patients will be monitored through a central venous line in the right or left jugular or subclavian vein and a Pulsioncath thermodilution catheter in left or right femoral artery.

#### Biological and pathological markers of ischemia

2.5.4

Blood and tissue samples will be collected at the 3 ROIs immediately after the 2 defined moments of ICGA. In order not to harm the conduit, no extra tissue will be resected compared to the standard Ivor Lewis procedure. Pathological specimen and tissue samples will be analyzed in the Department of Pathology at the University of Ghent. Biological specimens will be analyzed at the surgical research lab of the University of Ghent. Samples will be fully identified and stored at the research laboratory until the end of the study, thereafter they will be destroyed.

*The first biological marker is systemic and local capillary lactate:* systemic lactate will be measured on a blood gas sample during surgery at the beginning of the surgical procedure and at the 2 defined imaging moments. Tissue capillary lactate will be measured with a handheld lactate analyzer (EDGE Analyzer, Apex Biotechnology, Taiwan) at the same moments on blood samples obtained by a serosa puncture at the 3 ROIs.^[23,24,26]^

*The second marker of ischemia is the mitochondrial respiratory chain assessment*: Mitochondrial activity will be measured on full-thickness stomach biopsies at the previously marked ROIs. Samples will be placed in a 2-mL water jacketed oxygraphic cell equipped with a Clark type electrode (Oxygraph-2k, Ororboros Instruments, Innsbruck, Austria). Basal oxygen consumption and maximal tissue respiration rates at 37°C in the presence of a saturating amount of adenosine diphosphate as phosphate acceptor will be measured.^[23,24,26]^

*Finally, pathological analyses* will be performed on the biopsies at the 3 ROIs after they will be buffered in formalin and stained with hematoxylin and eosin. A semiquantitative scoring based on the presence of fibroblasts, polynuclear neutrophils, lymphocytes, and macrophages will be used to evaluate the severity of the inflammation. Further planned analyses (in addition to standard histology: TNM 7, Mandard regression score) include fluorescence in situ hybridization of the *MDM2* gene and immunohistochemistry analyses of ischemia-associated proteins HIF-1α, MDM2, CDK4, and p16.^[23,24,26–30]^

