### Study design

2.1

This is a prospective, single-center, in vivo, observational study on 70 patients undergoing minimally invasive esophagectomy (MIE) with a pedicle gastric graft reconstruction in the department of digestive surgery at the University Hospital of Ghent. ICGA images perfusion measurements, blood samples, and biopsies will be obtained after creation of the gastric tube and before the esophagogastric anastomosis. Dynamic ICGA digital images will be obtained and subjected to curve analysis and to compartmental analysis based on the adiabatic approximation to tissue homogeneity (AATH) kinetic model. The calculated imaging based perfusion assessment of the stomach graft will be compared to intraoperative hemodynamic data and validated using tissue, serum, and cellular hallmarks of hypoperfusion and hypoxia. Finally, the ability of functional, histological, and cellular perfusion and oxygenation parameters to predict AL and postoperative morbidity in general will be evaluated using the appropriate univariate and multivariate statistical analyses.

The methodology was developed according to the strengthening the reporting of observational studies in epidemiology (STROBE) and the statement for reporting studies of diagnostic accuracy (STARD) guidelines. The protocol was written based on the Standard protocol items for clinical trials (SPIRIT) checklist.

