#### Data analysis

2.6.4

The quantitative imaging data will then be correlated with chemical and pathological markers of ischemia (Capillary lactate levels, mitochondrial chain respiratory rates, histopathological assessment, and immunohistochemical markers of ischemia) and with postoperative morbidity and mortality, including radiological or clinical AL (recorded and scored using the Clavien-Dindo scale). Based on a receiver operating curve we hope to determine a cut-off value for the prediction of gastric graft malperfusion, based on the Youden index.

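### At the planned sampling times, and with no pre-graft tissue sample, the chronic-cell histology and MDM2 FISH are weak references for acute graft ischemia

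*Protocol article*

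**What the plan says.** All references are to the protocol article.

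- **Timing.** Section 2.5.2 sets two imaging moments: "30 minutes after the creation of the stomach graft (in the abdomen), and immediately before creation of the esophagogastric anastomosis". Section 2.5.4 ties sampling to them: "Blood and tissue samples will be collected at the 3 ROIs immediately after the 2 defined moments of ICGA". Section 2.1 confirms that "biopsies will be obtained after creation of the gastric tube and before the esophagogastric anastomosis". The time from graft creation to the second moment is not given.
- **Markers.** Besides lactate and mitochondrial respiration, section 2.5.4 plans a histology score: "A semiquantitative scoring based on the presence of fibroblasts, polynuclear neutrophils, lymphocytes, and macrophages will be used to evaluate the severity of the inflammation". Listed as further analyses are "fluorescence in situ hybridization of the" MDM2 gene and "immunohistochemistry analyses of ischemia-associated proteins HIF-1α, MDM2, CDK4, and p16".
- **Use.** Section 2.2 makes validation of ICGA against lactate, mitochondrial respiration and histopathology a secondary endpoint. Section 2.6.4 states: "The quantitative imaging data will then be correlated with chemical and pathological markers of ischemia". Its bracketed list names capillary lactate, mitochondrial respiration, histopathology and immunohistochemistry.
- **Baseline and sites.** A value from the start of surgery is described only for systemic lactate. In section 2.5.1 (Figure 1), ROI 1 is near the pylorus and is the well-perfused control, ROI 2 is the intended anastomotic site, and ROI 3 is in the proximal stomach and is the ischemic control.

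**The concern.** A reference marker for acute graft ischemia has to be able to move between the onset of ischemia and the moment of sampling. Some of the listed markers are unlikely to do so in one operation. If they do not move, they describe the stomach as it was before surgery.

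The design cannot correct for this, because no tissue is taken before the graft is made and the intended perfusion level goes together with anatomical site. Two misreadings are possible. If the regions do not differ in these markers, the result may be read as failed validation. If they already differed before surgery, the resulting correlation with ICGA may be read as successful validation. Neither result would say anything about graft ischemia.

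**Working it through.** There is no stated figure to reproduce. The check compares sampling time with what each marker can plausibly show.

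**1. Sampling window.** The first sample is at 30 minutes (sections 2.5.2 and 2.5.4). The second is unstated. As an assumption, take about one to several hours, since it falls in the same operation and before the anastomosis.

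**2. Markers against that window.** Response times are general biology, not taken from the article.

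| Marker in 2.5.4 | Plausible acute change by sampling? |
|---|---|
| Capillary lactate | Yes |
| Mitochondrial respiration | Yes |
| HIF-1α (immunohistochemistry) | Yes |
| Neutrophils (part of the score) | Possibly, more so at the second sample |
| Fibroblasts, lymphocytes, macrophages (part of the score) | Unlikely at 30 minutes or over several hours |
| MDM2 FISH (gene copy number) | Not expected |
| MDM2, CDK4, p16 (immunohistochemistry) | Not established by the article |

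Counting single items: 4 can plausibly respond, 3 chronic cell types and 1 FISH result are unlikely to, and 3 proteins are open, so 4 + 3 + 1 + 3 = 11. Within the histology score, 3 of 4 components are in the unlikely group.

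**3. What a comparison between ROIs can show.** Write a marker at ROI r and time t as Y(r,t) = S(r) + D(r,t). S is the level before surgery at that site and D is the response to graft ischemia. Then

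Y(3,t) − Y(1,t) = [S(3) − S(1)] + [D(3,t) − D(1,t)].

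If D is close to zero, only S(3) − S(1) remains. S could be estimated from tissue taken before graft creation, but none is described. The size and direction of S(3) − S(1) are not known from the article; it may be zero.

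**4. What a correlation within one ROI can show.** Section 2.6.4 does not state the unit of correlation. If it is across patients at one ROI, site is held fixed. With D close to zero, however, the marker still varies only with each patient's prior tissue state, so the correlation again does not reflect a response to ischemia.

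**5. Pooling.** A single score adds the neutrophils, which may respond, to three cell types that probably do not. The article gives no weights. Under any weighting that includes the three, they add variation unrelated to acute ischemia and dilute the neutrophil signal.

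**6. What the two moments offer.** Where an ROI has tissue at both,

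Y(r,t2) − Y(r,t1) = D(r,t2) − D(r,t1).

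S cancels, which is useful for the fast markers. Any response that occurred before t1 also cancels, because t1 already follows graft creation. This is not a change from a pre-ischemic baseline.

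**The case against.** The strongest reply is that the kinetics come from outside the article. It gives no response times, it cites references for these markers that cannot be examined here, and the second interval is unstated. That stands as a limit on certainty. A reader might infer that the markers cannot respond, or that they will show pre-existing regional differences. The documents support neither: the first is a biological inference, and the markers may equally show no difference at all.

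Second, the text is narrower than it first looks. Section 2.6.4 does not name FISH and does not say that correlations run across ROIs. In section 2.5.4 the cell score is described as a measure of inflammation, and the label linking markers to ischemia is attached to the proteins, not to FISH. This stands too. For FISH, the point is therefore a request to state its status. For the cell score the objection does not remove the problem, because section 2.6.4 lists histopathological assessment among the markers of ischemia.

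Third, a reader might take the planned Mandard score as a sign of preoperative treatment, suppose radiotherapy, and infer a proximal-to-distal gradient of old inflammation. Radiotherapy is not mentioned anywhere in the article, and the point does not need it.

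Fourth, weighting of markers and modelling by ROI are details that an article may leave to a fuller document. That is fair for the modelling. The marker set, sampling times and sites are stated here, and an analysis plan cannot change when tissue was taken.

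**Conclusion.** The point holds in a limited form. Fibroblast, lymphocyte and macrophage infiltration and MDM2 gene copy number are weak references for acute graft ischemia as sampled. Differences between ROIs in them could not be attributed to ischemia, and a lack of difference would not be evidence against ICGA.

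This rests on two statements in the article, namely that all tissue follows graft creation within one operation and that the ROIs lie at different sites, and on its description of no pre-graft tissue sample. It also rests on one assumption, that these markers do not change materially between 30 minutes and several hours.

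The extent is three of four components of one score, plus one gene-level test whose role is not stated. A reader might infer that the whole validation fails. It does not: lactate, mitochondrial respiration, HIF-1α and possibly neutrophils remain usable. The primary endpoint, an ICGA time cutoff for leakage and graft necrosis, does not depend on these markers.

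**What to change.** In sections 2.5.4 and 2.6.4:

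1. Score neutrophils separately from fibroblasts, lymphocytes and macrophages.
2. Report those three cell types as background tissue state, either as an exploratory result or as a covariate, and not as markers of ischemia that validate ICGA.
3. State that MDM2 FISH is exploratory and outside the validation set.
4. Base the validation claim on capillary lactate, mitochondrial respiration, HIF-1α and neutrophils. Label MDM2, CDK4 and p16 immunohistochemistry exploratory unless a response within the sampling window is justified.
5. Where an ROI has tissue at both moments, add the within-ROI change as a supportive analysis, and say that both samples follow graft creation.

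The cost is protocol and analysis wording, plus separate recording of the cell types when slides are read. Sampling and imaging stay as planned. The drawback is that fewer markers support the validation claim.

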### Follow-up and data collection and management

2.6

#### Follow-up

2.6.1

Primary follow-up will be up to 30 days with clinical evaluations daily and radiological evaluations based on the standard of care of the department, and outpatient clinic follow-up visits at 30 to 60 days postoperatively. Extended follow-up will be foreseen until 1 year postoperatively for stricture.

#### Data collection

2.6.2

All data will be retrieved from the electronic medical database and collected on Clinical Research File sheets. Three-minute long video files of the ICGA will be stored on a computer and analyzed with AMIDE ROI software (http://amide.sourceforge.net).

#### Image analysis

2.6.3

Image analysis will be performed using curve analysis and compartmental modeling. First, intensity over time curves will be analyzed in the ROIs to generate quantitative values for maximal fluorescence intensity (*I*_max_), inflow time (*T*_inflow_), and outflow time (*T*_outflow_). Second, a kinetic modeling analysis of the time-varying ICG concentration images will be performed. This analysis will be based on a tracer kinetic model that was developed to measure tissue blood flow and vascular permeability and that has been used previously to assess vascular parameters in a tumor mode and in the brain.^[31,32]^ This complex model (AATH) will be applied on the extracted maps of perfusion and vascular permeability from the video frame rate images acquired after a bolus injection of ICG. The arterial input function of ICG, which is required for modeling, will be extracted from the images by identifying the gastric artery. This analytic work will be done in collaboration with the Imaging Division, Lawson Health Research Institute, London, Ontario.

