### NIRF imaging with ICG

1.3

Indocyanine green angiography (ICGA) is an emerging medical imaging modality requiring a fluorescence-imaging agent that can be excited at near infrared (NIR) wavelengths. Penetrating NIR light excites a near-infrared fluorescence (NIRF) agent generating fluorescence that can be captured by adapted cameras to create a 2D image of tissue deposition of the NIRF imaging agent. Indocyanine green (ICG) is a clinically used NIRF agent with excellent safety records. Its absorption maximum around 760 to 780 nm, its confinement to the vascular compartment (due to binding with plasma proteins), its low toxicity, and its rapid and almost exclusive biliary excretion has added to the rapid Food and Drug Administration approval for clinical use in 1956. ICG has been used intraoperative in neurosurgical, coronary, vascular, and reconstructive surgeries as a nonspecific blood vascular imaging agent to assess organ perfusion.^[16]^

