### Study objectives and endpoints

2.2

The primary endpoint will be to determine an ICGA-based cutoff point to predict AL and graft necrosis after esophageal reconstructive surgery. This cutoff value will be an ICGA fluorescent intensity time measurement expressed in seconds.

Secondary endpoints are the following:

The evaluation of ICGA as a quantitative perfusion imaging modality during gastric tube reconstruction. First, intensity over time curves will be analyzed in the regions of interest to generate quantitative values for maximal fluorescence intensity (*I*_max_), inflow time (*T*_inflow_), and outflow time (*T*_outflow_). Second, a kinetic modeling analysis of the time-varying ICG concentration images will be performed, based on a tracer kinetic model that was developed to measure tissue blood flow and vascular permeability.The validation of ICGA imaging by comparing the quantitative data:

To continuous perioperative hemodynamic measurements from a Pulse index Continuous Cardiac Output (PiCCO) catheter.To biological markers of hypoxia and ischemia: systemic and capillary lactate levels (measured in systemic and serosal blood samples) and mitochondrial chain respiratory rates (measured on tissue biopsies).And to histopathological ischemic markers of hypoxia and ischemia.Patient outcome in terms of AL and necrosis defined by the Esophagectomy Complications Consensus Group (ECCG) classification and identified by clinical and radiological methods. Based on a receiver operating curve we hope to determine a cut-off value for the prediction of gastric graft malperfusion.Product-related toxicity.Surgery-related endpoints: number of crossover patients: perioperative change of anastomotic site based on ICG findings, perioperative blood loss, and perioperative adverse events.Incidence of minor and major adverse events up to 30 days postoperatively classified by the Clavien-Dindo score and based on the ECCG international consensus for complications associated with esophagectomy.^[25]^Intensive care unit and in hospital stay and finally incidence of stricture up to 1 year postoperatively.

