## Discussion

3

Esophageal anastomoses are fragile and prone to leakage, which is associated with significant morbidity, mortality, and impaired quality of life. The perfusion of the anastomosis is generally considered to be an important predictor for anastomotic integrity. During surgery the clinical judgment of the surgeon determines the anastomotic region based on subjective parameters. A good noninvasive method to objectively assess viability and both macro- and microvascular perfusion of the anastomotic site could help the surgeon to reliably decide the appropriate anastomotic region. Such a test needs to be easily available, cost effective, objective, and reproducible. NIRF imaging with ICG might combine all these advantages but is not yet calibrated nor validated. The proposed clinical study would be the first to use NIRF dynamic images to calculate physiologically relevant parameters (blood flow, blood volume, vascular leakage) and generate pseudocolor coded parametric maps using advanced curve analysis and compartmental modeling (AATH model).^[26,31]^ In addition, this study would be the first to validate imaging-based perfusion assessment of the stomach graft using tissue, serum, and cellular hallmarks of hypoperfusion and hypoxia. Data from this study will result in quantification of ICGA images, evaluate its potential to assess graft perfusion, and analyze its impact on AL after MIE for EC. The results of this project may allow to predict, and therefore avoid, AL after EC surgery. This may, in turn, prevent the morbidity and mortality associated with AL. Also, the results might contribute to a better understanding of gastric graft perfusion and oxygen supply in EC surgery.

In conclusion, this study will produce quantitative perfusion-related measurements for an objective ICGA assessment of tissue perfusion during surgery. The insights gained and the methods developed during this project may also benefit patients undergoing other types of cancer surgery (rectum, pancreas…) in which anastomotic tissue viability is of critical importance.

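### Vascular leakage is derived with AATH from a dye described as intravascular, with no check that spread in transit times is not read as extraction

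*Protocol article*

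**What the plan says.** Section 1.3 (NIRF imaging with ICG) lists among the dye's merits "its confinement to the vascular compartment (due to binding with plasma proteins") and says it has been used "as a nonspecific blood vascular imaging agent to assess organ perfusion".

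Section 2.2 (Study objectives and endpoints) makes kinetic modelling part of a secondary endpoint, "based on a tracer kinetic model that was developed to measure tissue blood flow and vascular permeability". Section 2.6.3 (Image analysis) says "This complex model (AATH) will be applied on the extracted maps of perfusion and vascular permeability". I read permeability maps there as a product of the analysis, although the sentence could be taken to make them its input. On the input function it says: "The arterial input function of ICG, which is required for modeling, will be extracted from the images by identifying the gastric artery".

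Section 2.5.2 fixes the observation window: "Images will be recorded starting immediately before injection until 3 minutes afterwards".

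Section 3 (Discussion) says the study will "calculate physiologically relevant parameters (blood flow, blood volume, vascular leakage") from the dynamic images. Section 2.6.4 (Data analysis) correlates the quantitative imaging data with lactate, mitochondrial respiration, histology, immunohistochemistry and postoperative morbidity, including anastomotic leakage.

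**The concern.** A dye that stays in the vessels carries no information on permeability. A model with a permeability term will nevertheless return a value for it. AATH treats vascular passage as plug flow: all dye leaves after one transit time. Any later tail is assigned to dye that has crossed the vessel wall. Real vascular beds have a spread of transit times, so late-leaving intravascular dye also makes a tail, and plain AATH has nowhere else to put it.

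The graft is studied because flow may be poor, and the protocol samples an ischaemic control region. Slow transit is therefore the situation of interest. If slow transit raises fitted extraction, a correlation of leakage with lactate, histology or anastomotic leak could be reported as ischaemic vascular damage when it reflects slow flow only. The validation aim would then rest on a mislabelled quantity.

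**Working it through.** The plan gives no figure to reproduce here, so the check is of the mechanism.

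**Inputs.** From the protocol: a 180 s window (section 2.5.2), the AATH model (sections 2.1 and 2.6.3), and the intravascular description of the dye (section 1.3). Assumed, because the article does not give them: a bolus input with recirculation; gamma-distributed vascular transit times with stated mean and coefficient of variation (CV); for the noisy runs, 1 Hz sampling and 3% noise; for a true leak, a washout rate k of 0.002/s.

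**Model fitted.** The tissue curve is flow F times the convolution of the input with R(t), where R(t) = 1 up to transit time Tc and R(t) = E·exp(−k(t − Tc)) afterwards. F, Tc, E (between 0 and 1) and k are free. This is the usual AATH form; the article does not write it out.

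**Step 1: a case that needs no simulation.** With CV = 1 the transit times are exponential and the intravascular residue is exp(−t/MTT), where MTT is the mean transit time. AATH reproduces this exactly with Tc → 0, E = 1 and k = 1/MTT. True extraction is zero, fitted extraction is 1, and the fit is perfect.

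**Step 2: zero leakage, no noise.** With mean transit 5 or 10 s and CV 0.25 to 1.0, fitted E was 0.96 to 1.00, k was about 0.10 to 0.87/s, and the residual was at most 0.4% of peak, so poor fit would not expose the error. At CV 0.05 (near plug flow), E ranged from 0.10 to 0.84 with k on its upper bound of 2/s, so E was not identifiable. Noisy runs with pure plug flow (CV 0) gave a median E of about 0.

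**Step 3: a real leak, no noise, mean transit 8 s.** True E of 0.03 was fitted as 0.030 (CV 0.05) or 0.051 (CV 0.5). True E of 0.10 was fitted as 0.100 or 0.130. Fitted k was about 0.002 to 0.006/s. Here AATH does its job.

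**Step 4: slower transit, with noise.** Median fitted E, 8 replicates per setting:

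| Mean transit, CV | True E 0 | True E 0.03 | True E 0.10 |
|---|---|---|---|
| 8 s, 0.5 | 1.00 | 0.06 | 0.14 |
| 8 s, 1.0 | 0.98 | 0.18 | 0.22 |
| 20 s, 0.5 | 1.00 | 1.00 | 0.23 |
| 20 s, 1.0 | 0.87 | 0.68 | 0.46 |
| 30 s, 0.5 | 1.00 | 1.00 | 0.42 |
| 30 s, 1.0 | 0.92 | 0.79 | 0.64 |

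A separate repeat gave 0.95 to 1.00 for true E = 0, and 0.55 to 1.00 for true E = 0.03 at 20 s.

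Three things follow.
- At 20 to 30 s the inflation runs from 0.23/0.10 = 2.3-fold to 1.00/0.03 = 33-fold.
- At a fixed true E of 0.03 and CV 0.5, moving from 8 s to 20 s takes fitted E from 0.06 to 1.00. Transit alone moves the leakage value.
- Across a row, fitted E mostly falls as true leakage rises, so E on its own can rank regions in the wrong order.

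**Step 5: does k expose the artefact?** In the leak settings at 20 to 30 s, fitted k was 0.011 to 0.068/s against a true 0.002/s. By step 1, zero leak with CV = 1 gives k = 1/20 = 0.05/s at 20 s and 1/30 = 0.033/s at 30 s, inside that same range. So k separates the cases at 5 to 10 s but not at slow transit.

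**Step 6: blood flow.** With zero leak, fitted F was 0.90 to 1.00 of true without noise, and about 4 to 14% low with noise. With a leak it was 0.84 to 1.00 without noise (8 s) and 0.68 to 0.97 with noise across the settings in the table.

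**The case against.** The strongest case against has five parts.

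- **No true contradiction.** Confinement is given as a general property of the dye, in an introduction. Nothing is said about ischaemic or handled stomach. A tracer normally held in the vessels may be a sensible probe for abnormal leak. This stands: the documents neither establish nor exclude leakage in the graft. A reader might infer that true extraction is zero everywhere, and hence that the reported leakage must be an artefact. The text does not support that.
- **Real leaks are recovered, and k distinguishes them.** True for fast transit with little or moderate spread (step 3). It fails at slow transit (steps 4 and 5), which matters most in a study of poor perfusion.
- **A distributed-transit model looks better only because it generated the curves.** In zero-leak simulations such a model recovered flow and mean transit time within about 3% and had the lower AIC in 85 to 100% of fits. That comparison is partly circular. It does not show that the model suits real graft curves or justify replacing AATH.
- **Fitting rules belong in a fuller document.** Fair for bounds, starting values and software. But the model and its leakage output are stated outright, and the output is promised without condition.
- **Small impact.** Largely right. Section 2.2 uses permeability to describe what the model was developed for, and section 2.6.4 assigns no causal reading to the correlations.

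**Conclusion.** The point holds as a possible error with no stated safeguard, not as a certain one. The article derives permeability or leakage from a dye it describes as intravascular and does not say how non-zero extraction will be distinguished from spread in transit times. Under the assumptions above, fitted E is near 1 at zero leakage once spread is moderate or wide, and is strongly inflated for a small leak with slow transit. Inflation shrinks as the leak grows, and recovery is good when transit is fast with little spread.

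The size depends on transit means, spreads, input function and noise that the documents do not give, and the noisy medians rest on few replicates. Direction and mechanism are firmer than any single value.

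The reach is limited. Only the permeability output of a secondary endpoint is seriously affected. Flow bias is mostly modest, though larger with wide dispersion plus a leak. A reader might extend the criticism to the primary endpoint, but that is a fluorescence time in seconds taken from the intensity curve; it, its ROC analysis and the sample size do not use the AATH extraction estimate. The change is recommended rather than essential.

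**What to change.** In section 2.6.3, keep AATH and add a comparator fitted to the same curves: an intravascular model (E = 0) with distributed transit times, fitted with and without an extraction term.

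- Report extraction or permeability for a region of interest only where the extraction term improves the fit by a criterion set in advance, for example AIC. Otherwise report it as not estimable.
- Report blood flow and mean transit time from both models as a sensitivity check.
- In section 3, make vascular leakage a conditional or exploratory output, and add a sentence reconciling it with the intravascular description in section 1.3.

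The cost is a second fit to curves already extracted and a few lines of text, with no extra patients, procedures or images. The downside is that permeability may prove not estimable in many regions.
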